***Specific statistical analysis***

# *Statistical Analysis for primary endpoints*

**INTESTINAL INFLAMMATION:** The binary outcome variable is the presence of at least one intestinal inflammation episode for subject j in cluster i (i=1,..,N, j=1,…n). Based on the results of Bruzzese et al[6], a proportion of subjects with at least 1 episode of intestinal inflammation of 0.90 is expected; a reduction of 30% of such proportion is considered clinically relevant (0.90 vs 0.63). These values determine an odd of experiencing at least one intestinal inflammation episode 0.19 times smaller in the treatment group than in the control group. A intra-cluster correlation coefficient () between the two time occasions of 0.6 is assumed (this is rather a cautionary value because a smaller coefficient is expected) With a one-sided  of 0.025 and a statistical power (1-β) of 0.80, 35 subjects per treatment group are needed to detect such difference in favour of the LGG compared to placebo after twelve months. Alternatively, by using the sample size obtained for powering the analysis of pulmonary exacerbations, all other things being equals, a power of 92% will be reached.

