***Study design***

Study activities are reported in the timeline (Table 1).

| **Parameters** | **Visit 1a** | **Visit 2b** |
| --- | --- | --- |
| Written informed consent | x |  |
| Randomization |  | x |
| Clinical examination | x | x |
| Genetic analysis (if not already performed) | x |  |
| Demographic | x |  |
| Anthropometric | x | x |
| Intestinal inflammation | x | x |
| Microflora |  | x |
|  |  |  |

Study design

Patients meeting the inclusion criteria will be enrolled and randomly assigned to the treatment or placebo group arm. Patients randomized to the treatment arm will receive 6x109 CFU of LGG once a day for a 1-month period. Patients randomized to the placebo group will receive placebo once a day for 1 months. LGG and placebo formulations will be masked and coded appropriately to ensure blindness. LGG formulations will be composed of maltodextrin (163 mg), gelatine capsule (75 mg), LGG (60 mg), magnesium stearate (2 mg). The placebo composition will be maltodextrin (223 mg), gelatine capsule (75 mg) and magnesium stearate (2 mg). LGG and placebo capsules will be identical in appearance, taste and color and only a numeric code will differentiate the two formulations.

For these patients systemic inflammation and intestinal microflora using Fluorescent in situ Hybridization will be evaluated before starting treatment and at the end of it (0 and 1 month

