***Endpoints***

Primary endpoints:

- Modification of intestinal inflammation
- Modification of intestinal microflora composition

***Methods*** .

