**Intestinal inflammation**

Intestinal inflammation status will be monitored in a non-invasive manner.

At each scheduled time point, one stool sample will be collected and frozen at -20°C for fecal calprotectin analysis. Fecal calprotectin levels will be measured, using a standardized technique, in each participating center.

Fecal calprotectin concentration will be evaluated using the ELISA method (Calprest Eurospital, SpA, Trieste, Italy). Briefly, 0.1 g of feces are suspended in a buffer, pre-diluted, homogenized and centrifuged. The supernatant is collected and analyzed by an ELISA (according to the manufacturer’s instructions) with a specific polyclonal antibody. The reference values of fecal calprotectin range between 0 and 50 micrograms/g, values between 50 and 100 micrograms/g are considered intermediate, and require follow-up, whereas values over 100 micrograms/g indicate intestinal inflammation.

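### The any-episode primary endpoint and its sample size do not fit a 1-month trial with one stool before treatment and one at its end

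*Protocol*

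**What the plan says.** The statistical section for the primary endpoints defines the inflammation outcome as follows: "The binary outcome variable is the presence of at least one intestinal inflammation episode for subject j in cluster i". It states that "a proportion of subjects with at least 1 episode of intestinal inflammation of 0.90 is expected" and takes a relative reduction of 30%, to 0.63, as clinically relevant. It assumes that a correlation "between the two time occasions of 0.6 is assumed", and with one-sided alpha 0.025 and 80% power it obtains 35 per group for a difference at twelve months.

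The rest of the protocol describes a different structure:
- *Type of study/setting* gives a treatment phase of 1 month.
- Table 1 under *Study design* has two inflammation assessments, one per visit ("Intestinal inflammation | x | x"). The text below the table puts the evaluations ahead of treatment and at its end, at 0 and 1 month. That sentence says systemic inflammation, while the table row says intestinal.
- *Intestinal inflammation* under Methods provides one stool per time point and says that "values over 100 micrograms/g indicate intestinal inflammation".
- *Endpoints* lists "Modification of intestinal inflammation".

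The protocol does not define an episode and does not say whether the stool taken before treatment counts towards the outcome.

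**The concern.** An any-episode endpoint suits a trial with several assessments on treatment. Here the schedule offers only two occasions, and one of them precedes the first capsule. If the two occasions in the sample-size paragraph are these two stools, the outcome mixes a measurement that treatment cannot affect with one that it can. That sets a floor under both arms and shrinks the difference. If they are not these two stools, they do not exist in the schedule, and the correlation and the twelve-month horizon describe something the trial does not do. In either case the primary outcome cannot be derived without guessing, and the basis for 35 per arm does not match the data to be collected.

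**Working it through.** **Inputs.** From the statistical section: 0.90 versus 0.63, one-sided alpha 0.025, power 0.80, correlation 0.6 over two occasions, 35 per arm. From the schedule: one stool before treatment and one at 1 month. Assumed, because the protocol does not give it: baseline prevalence b, equal in both arms.

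**Step 1: the plan's own figure.** The odds ratio is (0.63/0.37)/(0.90/0.10) = 0.189, which matches the stated 0.19, and its logarithm is -1.665. With (1.960 + 0.842)² = 7.849, the log-odds-ratio formula for one occasion gives

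n = 7.849 × [1/(0.90×0.10) + 1/(0.63×0.37)] / 1.665² = 7.849 × (11.11 + 4.29) / 2.772 = 43.6.

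Multiplying by (1 + 0.6)/2 = 0.80 for two occasions gives 34.9, so 35. The unpooled difference formula with no correlation gives 7.849 × (0.090 + 0.2331)/0.27² = 34.8, also 35. The stated number is therefore reproducible, but the protocol does not show which route was used. The first route credits both occasions with the full treatment effect, which a stool taken before treatment cannot carry.

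**Step 2: both scheduled stools count.** With 1-month prevalence f and correlation phi between the two results,

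P(any) = b + f - P(both), where P(both) = b·f + phi·√[b(1-b)f(1-f)], and P(both) cannot exceed the smaller of b and f.

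Hence P(any) is never below b. Take f = 0.90 on placebo and 0.63 on LGG. Power below is exact chi-square power at 35 per arm.

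| Assumed b | P(any), phi = 0 | P(any), phi = 0.6* | Power over phi 0 to 0.6 |
| --- | --- | --- | --- |
| 0.90 | 0.990 vs 0.963 | 0.936 vs 0.900 | 3-13% |
| 0.80 | 0.980 vs 0.926 | 0.908 vs 0.810 | 14-22% |
| 0.70 | 0.970 vs 0.889 | 0.900 vs 0.756 | 27-36% |
| 0.50 | 0.950 vs 0.815 | 0.900 vs 0.670 | 44-67% |

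*Capped where 0.6 is not attainable for the two prevalences. For b = 0.90 the cap in the LGG arm is about 0.435.

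For b = 0.90, power is 2.8% at phi = 0, 8.5% at 0.2, 12.9% at 0.43 (0.951 vs 0.901) and about 8-9% at the plan's 0.6 with the LGG arm capped. In every row the difference is below the planned 0.27; the largest is 0.230, at b = 0.50.

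**Step 3: only the 1-month stool counts.** The contrast is then 0.90 versus 0.63 on one occasion. For 80% power this needs 35 per arm (unpooled), 38 (pooled) or 44 (log-odds-ratio, 43.6 rounded up). At 35 per arm the pooled chi-square test has 77% power by normal approximation and 78% exactly. The correlation of 0.6 does not enter.

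**The case against.** Nothing in the protocol states that the stool taken before treatment counts. The twelve-month horizon, and a reference to a pulmonary-exacerbation sample size that is not given here, could mean that the paragraph was written for a longer design with two assessments on treatment. That is plausible but the documents do not prove it. If true, it confirms the mismatch.

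A reader might infer that LGG cannot bring the endpoint below 0.90 and that power is therefore only 3-13%. The documents do not support this. The 0.90 is given as the any-episode rate, not as a prevalence before treatment, and the only baseline information is a mean calprotectin four times above normal. Using 0.90 at both occasions also gives a placebo any-episode rate of 0.936 to 0.990, above the plan's own 0.90. If 0.90 is instead the rate over two occasions with equal prevalence p at each, then 2p - p² - phi·p(1-p) = 0.90 gives p of about 0.68 (phi = 0) to 0.85 (phi = 0.6). The LGG floor would then be 0.68 to 0.85. That still excludes 0.63, but leaves more room than a floor of 0.90.

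Two further inferences should not be pressed. The listed endpoint of a modification in inflammation is a general label and does not clearly contradict a binary outcome. The link from the 100 micrograms/g cut-off to the outcome may stand in an SAP that is not shown.

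**Conclusion.** The point stands as a mismatch between the primary endpoint with its sample size and the trial's schedule. The protocol plans an any-episode outcome over two occasions at twelve months, and describes one stool before and one stool after 1 month of treatment. No reading reconciles these. Counting both stools dilutes the effect and leaves power at 35 per arm between about 3% and 67% for assumed baseline prevalences from 0.90 down to 0.50, always below 80%. Counting only the 1-month stool keeps the 0.27 contrast, with about 77-78% power by the pooled test, but removes the stated two-occasion basis. These figures assume 0.90 versus 0.63 at 1 month, equal baseline prevalence in the arms and phi from 0 to 0.6. Confidence is moderate, because the protocol does not say which stools count and gives no baseline prevalence.

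**What to change.** - Define the binary outcome as faecal calprotectin above 100 micrograms/g, the protocol's own cut-off for inflammation, in the end-of-treatment (1-month) stool. Compare the arms with baseline calprotectin as a covariate.
- Remove the any-episode wording, the subject-in-cluster notation, the two-occasion correlation and the twelve-month horizon from the sample-size paragraph. If the sponsor does intend longer follow-up, the paragraph and the 1-month schedule must be reconciled first.
- Confirm that the 0.90 planning rate refers to that cut-off and to a single time point.
- Restate the sample size for one post-treatment occasion and name the formula: 35 (unpooled), 38 (pooled) or 44 (log-odds-ratio) per arm for 80% power, or keep 35 and report about 77-78%.
- Align Table 1, which marks randomization at Visit 2, with the text that places the two evaluations before treatment and at its end.

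The cost is small. Both stools are already scheduled, so no new visits, samples or assays are needed. The stated power becomes slightly less favourable unless a few subjects per arm are added.

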**Experimental Design and Methods.**

***Type of study/setting***

This is a prospective, double-blind, randomized, pilot study comparing oral probiotics versus placebo. The total duration of the study will be 6 months:

- - Patients enrollment: 3 months
  - Treatment phase: 1 months
  - Data analysis and statistical evaluation: 2 months

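### The stated 35 per group and 80% power rest on a twelve-month horizon and two correlated occasions, and are not justified for a trial with one post-treatment sample at 1 month

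*Protocol*

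**What the plan says.** The sample size is in the Protocol, Statistical Analysis for primary endpoints, under intestinal inflammation. The outcome is binary: whether a child has at least one inflammation episode. The inputs are:

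- Control proportion: "a proportion of subjects with at least 1 episode of intestinal inflammation of 0.90 is expected".
- Effect: "a reduction of 30% of such proportion is considered clinically relevant (0.90 vs 0.63"), described as an odds "0.19 times smaller in the treatment group than in the control group".
- Correlation: a coefficient "between the two time occasions of 0.6 is assumed (this is rather a cautionary value because a smaller coefficient is expected").
- Level and power: one-sided 0.025 and 0.80.
- Result: "35 subjects per treatment group are needed to detect such difference in favour of the LGG compared to placebo after twelve months".

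The paragraph closes by claiming 92% power if the sample size for a pulmonary-exacerbation analysis is used instead. The Protocol contains no such analysis and no such sample size.

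The design sections differ. Type of study/setting gives "Treatment phase: 1 months" within a six-month pilot study. Study design says that the laboratory measures "will be evaluated before starting treatment and at the end of it (0 and 1 month"), and Table 1 has two visits, with intestinal inflammation assessed at both. The Intestinal inflammation methods section takes one stool sample for calprotectin at each time point.

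**The concern.** Two features of the power paragraph have no counterpart in the schedule. A twelve-month difference cannot be observed in a six-month study with one month of treatment. A correlation between two occasions reduces the required number by averaging only when both occasions carry the treatment effect, and here the month-0 sample precedes treatment. The reference to an absent pulmonary-exacerbation calculation also suggests that the paragraph was written for another design.

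This is the only basis given for the size of the trial. If it stays as it is, a null result on a primary endpoint would be read as coming from a trial with 80% power, on a calculation made for something else.

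**Working it through.** **Inputs** (Statistical Analysis for primary endpoints): p1 = 0.90, p2 = 0.63, one-sided level 0.025 (z = 1.960), power 0.80 (z = 0.842), correlation 0.6, two occasions. (1.960 + 0.842)² = 7.849. No dropout is allowed for in the plan, and none is assumed here.

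**Step 1: the odds ratio.** (0.63/0.37)/(0.90/0.10) = 0.189, which agrees with the stated 0.19. Its log is −1.665, with square 2.772.

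**Step 2: reproduce the 35.** On the log-odds scale, for one occasion per child:

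n = 7.849 × [1/(0.90 × 0.10) + 1/(0.63 × 0.37)] / 2.772 = 7.849 × 15.401 / 2.772 = 43.6.

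If two equally informative occasions with correlation 0.6 are averaged, the variance is multiplied by (1 + 0.6)/2 = 0.8:

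43.6 × 0.8 = 34.9, so 35 per group, with 80.1% power at 35.

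This route uses every stated input. On the same route, 92% power would need 50.3, so about 51 per group. The Protocol does not give the sample size to which its 92% refers.

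**Step 3: one post-treatment sample per child.** Same proportions and level, 35 per group. The exact figures enumerate all outcomes and count two-sided p < 0.05 in favour of LGG.

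| Method | Power at 35 per group | Per group for 80% |
| --- | --- | --- |
| Fisher's exact, exact power | 70.0% | 42 (80.4%) |
| Log-odds Wald | 70.9% | 44 |
| Two proportions, pooled normal | 77.1% | 38 |
| Chi-square, exact power | 78.3% | 37 (81.0%) |
| Two proportions, unpooled normal | 80.2% | 35 (34.8) |

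The last row is 7.849 × (0.09 + 0.2331)/0.27² = 34.8. It also arrives at 35, but without the 0.6 or a second occasion.

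**Step 4: the correlation.** When two post-treatment occasions are averaged, the factor (1 + r)/2 grows with r, so a high r is the cautious choice, as the plan says. If the two occasions are months 0 and 1, the baseline can help only through adjustment, and a lower correlation then helps less. In that case a value higher than expected is not cautious.

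**The case against.** The strongest reply is that the Protocol names no formula and that a plain unpooled comparison of two proportions at one time point also gives 35 with 80.2% power. That stands, and it limits the claim. A reader might infer that true power must be well below 80%, and the documents do not support this: the loss runs from nothing to about 10 points, and under chi-square it is less than 2. But the unpooled formula leaves the stated correlation unused, and it does not explain the twelve months.

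A second reply is that the two occasions are months 0 and 1. The text does not say that both follow treatment, so this reading is open. It does not rescue the statement, because the averaging factor does not apply to a pre-treatment sample. Baseline adjustment could recover power: with the approximate variance factor 1 − r², which is an assumption because the Protocol specifies no adjusted model, log-odds power at 35 is about 88% at r = 0.6. The plan does not make that calculation.

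A reader might also infer that 0.6 is mathematically impossible, because binary proportions of 0.90 and 0.63 in the same children cap their correlation at about 0.43. That requires a baseline proportion of 0.90 in the LGG arm. The plan gives 0.90 as an expected proportion for the comparison with 0.63, not as that arm's baseline, so the argument is not relied on.

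Finally, chi-square and Fisher's exact test are named under the secondary-endpoint heading. That section covers intestinal inflammation, but no test is named for the primary analysis, so the figures for these tests are illustrations. That the study is called a pilot does not remove the problem: the Protocol chose to state a powered sample size.

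**Conclusion.** The point holds. The horizon and the two-occasion correlation in the power paragraph do not match a schedule with one month of treatment and one sample at each of months 0 and 1, so the stated 80% is not justified for this design. For one post-treatment sample, power at 35 per group is 70% to 80% depending on the method. Exact power first reaches 80% at 37 per group with chi-square and at 42 with Fisher's exact test; the log-odds formula needs 44.

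These figures take the plan's 0.90 and 0.63 as given, with equal groups and no dropout. Whether proportions defined as at least one episode carry over to a single 1-month sample cannot be checked from the Protocol. The inconsistency itself depends on none of these assumptions.

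**What to change.** - Reconcile the twelve-month horizon in Statistical Analysis for primary endpoints with the duration and sampling times in Type of study/setting and Study design.
- If the 0- and 1-month schedule stands, remove the two-occasion correlation, its description as cautionary, and the 92% sentence.
- Name the primary test and restate power at 35 per group for one 1-month sample under that test, for example about 78% with chi-square or 70% with Fisher's exact test.
- Alternatively, specify a baseline-adjusted analysis and derive the power for it, with the assumed correlation stated and varied.

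The cost is a short recalculation and a change of wording. No extra patients are needed to restate the figure. The drawback is a somewhat less favourable stated power under most of the methods.

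### The 92% power for intestinal inflammation is taken from the sample size of a pulmonary-exacerbation analysis that this protocol does not contain

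*Protocol*

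**What the plan says.** All of the sample-size reasoning stands in one paragraph of the Protocol, under Statistical Analysis for primary endpoints (intestinal inflammation).

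- Control rate: "a proportion of subjects with at least 1 episode of intestinal inflammation of 0.90 is expected".
- Effect: "a reduction of 30% of such proportion is considered clinically relevant (0.90 vs 0.63", described as "an odd of experiencing at least one intestinal inflammation episode 0.19 times smaller in the treatment group than in the control group".
- Correlation between the two time occasions: 0.6.
- Size: "With a one-sided" alpha "of 0.025 and a statistical power (1-β) of 0.80, 35 subjects per treatment group are needed".
- Last sentence, offered as an alternative: "by using the sample size obtained for powering the analysis of pulmonary exacerbations, all other things being equals, a power of 92% will be reached".

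Under Endpoints, the first of two primary endpoints is "Modification of intestinal inflammation" and the second is the change in microflora composition. Type of study/setting says: "This is a prospective, double-blind, randomized, pilot study comparing oral probiotics versus placebo".

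**The concern.** A power figure means something only with the sample size it belongs to. The size behind the 92% is not given. The reader is sent to an exacerbation calculation that the document does not hold. One primary endpoint therefore carries two powers, 80% and 92%, and the second has no stated size.

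At stake is whether the sample-size justification describes this trial. Because the last sentence is worded as an alternative, a reader cannot tell whether 35 per group or some larger number governs enrolment. Anyone who later cites 92% for a trial of 35 per group would be claiming power that the stated design does not have.

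**Working it through.** **Step 1. Look for the exacerbation analysis.**

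| Place in the Protocol | Content on pulmonary exacerbations |
|---|---|
| Endpoints | None; only inflammation and microflora |
| Study design, Table 1 | No exacerbation assessment at either visit |
| Statistical Analysis of Secondary Endpoints | None; only inflammation and fecal microflora |
| Significance | Background on an earlier cross-over study |
| Inclusion criteria | Acute exacerbation only, as part of clinical stability |

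No exacerbation rate, effect or sample size is given anywhere.

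**Step 2. Reproduce the 35 per group.** Inputs from the sample-size paragraph: p1 = 0.90, p2 = 0.63, one-sided alpha 0.025 (z = 1.960), power 0.80 (z = 0.842), correlation 0.6. Equal allocation is assumed, since one size is given for each group. No dropout allowance is stated, so none is applied.

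- Odds ratio: (0.63/0.37)/(0.90/0.10) = 0.189, which agrees with the stated 0.19. Its log is -1.665.
- (1.960 + 0.842)² = 7.849.
- Log-odds formula: 7.849 × [1/(0.90×0.10) + 1/(0.63×0.37)] / 1.665² = 7.849 × 15.401 / 2.772 = 43.6. With the two-occasion factor (1 + 0.6)/2 = 0.8 this is 34.9, so 35.
- Unpooled difference, one occasion: 7.849 × (0.09 + 0.2331) / 0.27² = 34.8, so 35.

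Both reproduce the stated 35. The pooled formula gives 38, or 45 with continuity correction. Applying 0.8 to the pooled or unpooled difference gives 30.0 or 27.8. None of these four matches.

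**Step 3. Back-calculate the size for 92%.** With z = 1.405 for power, (1.960 + 1.405)² = 11.323.

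| Formula | n per group for 92% |
|---|---|
| Log-odds × 0.8 (reproduces 35) | 50.3, so 51 |
| Unpooled, one occasion (reproduces 35) | 50.2, so 51 |
| Unpooled × 0.8 | 41 |
| Pooled × 0.8 | 43 |
| Pooled | 54 |
| Pooled, continuity-corrected | 61 |
| Log-odds, one occasion | 62.9, so 63 |

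The two formulas that match the plan agree on 51 per group, or 102 in total. That is 16 per group, about 46%, more than 35 (51/35 = 1.46). The second of them uses a single occasion, so the 51 does not depend on the two-occasion assumption.

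**Step 4. Power at 35 per group.**

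| Method | Power |
|---|---|
| Fisher's exact test | 70% |
| Log-odds, one sample | 71% |
| Pooled formula, one occasion | 77% |
| Chi-square test, exact power | 78% |
| Unpooled difference, one occasion | 80% |
| Log-odds × 0.8 | 80% |

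Applying 0.8 to the pooled or unpooled difference would give 86% or 88%. Those variants need only 30.0 or 27.8 per group for 80%, so they contradict the plan's own 35, and they still fall short of 92%.

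**The case against.** The strongest defence is that the sentence is conditional and harmless. The paragraph names 35 per group as the size needed for 80% power, the study is called a pilot, and removing the sentence changes no endpoint, test or stated size. That is fair as to the cost of the change. It does not supply the missing size. A separate statistical analysis plan would not help either, because the protocol itself relies on a calculation for an endpoint that it does not have.

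Four stronger readings are tempting, and the document does not support them:

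- **That 92% is miscalculated.** It is a possible power at about 51 per group. What is missing is its basis.
- **That 80% at 35 per group is unattainable with one post-treatment sample.** The unpooled one-occasion formula gives 80%.
- **That only 22 children were planned.** The section on FISH evaluation mentions 22 stable children with CF, but in the past tense and as the sample examined by FISH. It does not call them the planned size for the inflammation endpoint.
- **That a negative result would be presented as conclusive.** This could follow if 92% were cited beside it, but nothing in the document says so.

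The same paragraph expects the difference after twelve months, while treatment lasts one month. This fits text carried over from a longer trial. It is an inference, and the point does not need it.

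**Conclusion.** The point holds as an internal inconsistency. The protocol states a 92% power whose sample size belongs to an analysis that is absent from the document. At 35 per group, power is about 70% to 80% depending on the method, so 92% is not reached at the only per-group size given.

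The 51 per group is an assumption, because the plan does not name its formula. It rests on the stated 0.90 and 0.63, one-sided 0.025, equal groups and no dropout. The range is about 41 to 61 over the variants on the difference in proportions, and 63 for log-odds with one occasion. The conclusion does not depend on which variant is right, since the protocol plans none of these sizes.

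**What to change.** Delete the last sentence of the intestinal-inflammation paragraph, from its opening word Alternatively to the 92% claim. State one planned size per group and one power figure, computed for this trial's own inflammation endpoint with the test that will be used, and name the formula. If a larger enrolment than 35 per group was intended, give that number as the single planned size, with its basis.

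Deleting the sentence costs only wording: no endpoint, test or stated size changes, and a favourable power figure is withdrawn. If the power is restated for the chi-square or Fisher test at 35 per group, it will read 78% or 70% instead of 80%.
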